## Abstract

**Background:**

Disease management programmes (DMPs) have been shown to reduce hospital readmissions and mortality in adults with heart failure (HF), but their effectiveness in elderly patients or in those with major comorbidity is unknown. The Multicenter Randomised Trial of a Heart Failure Management Programme among Geriatric Patients (HF-Geriatrics) assesses the effectiveness of a DMP in elderly patients with HF and major comorbidity.

**Methods/Design:**

Clinical trial in 700 patients aged ≥ 75 years admitted with a primary diagnosis of HF in the acute care unit of eight geriatric services in Spain. Each patient should meet at least one of the following comorbidty criteria: Charlson index ≥ 3, dependence in ≥ 2 activities of daily living, treatment with ≥ 5 drugs, active treatment for ≥ 3 diseases, recent emergency hospitalization, severe visual or hearing loss, cognitive impairment, Parkinson's disease, diabetes mellitus, chronic obstructive pulmonary disease (COPD), anaemia, or constitutional syndrome. Half of the patients will be randomly assigned to a 1-year DMP led by a case manager and the other half to usual care. The DMP consists of an educational programme for patients and caregivers on the management of HF, COPD (knowledge of the disease, smoking cessation, immunizations, use of inhaled medication, recognition of exacerbations), diabetes (knowledge of the disease, symptoms of hyperglycaemia and hypoglycaemia, self-adjustment of insulin, foot care) and depression (knowledge of the disease, diagnosis and treatment). It also includes close monitoring of the symptoms of decompensation and optimisation of treatment compliance. The main outcome variables are quality of life, hospital readmissions, and overall mortality during a 12-month follow-up.

**Discussion:**

The physiological changes, lower life expectancy, comorbidity and low health literacy associated with aging may influence the effectiveness of DMPs in HF. The HF-Geriatrics study will provide direct evidence on the effect of a DMP in elderly patients with HF and high comorbidty, and will reduce the need to extrapolate the results of clinical trials in adults to elderly patients.

**Trial registration:**

(ClinicalTrials.gov number, NCT01076465).

## Background

Ninety percent of persons with incident heart failure (HF) are age 65 or over; moreover, the prevalence of HF increases with age, rising from 5-10% in persons aged 65-79 years to 10-20% in those 80 years or over [1]. In Spain, about 500,000 persons over the age of 60 suffer from HF [2]. HF is the most frequent reason for hospital admission and readmission [3] and is the third leading cause of cardiovascular death in the elderly [4]. Moreover, it represents about 2% of total health costs [5]. The number of hospitalisations for HF is expected to increase up to 50% in the next 20 years [6].

HF produces physical and cognitive impairment as well as reduced quality of life [7-9]. Annual mortality exceeds 50% in patients with New York Heart Association (NYHA) classes III and IV [10]. Advanced age, as well as low quality of life and poor social network - two variables which are not routinely assessed in patients - are all associated with a higher risk of hospitalisation and death in HF [11,12].

Treatments are available to modify the course of HF with left ventricular systolic dysfunction (LVSD) [13,14], but they have not managed to significantly reduce mortality and hospital readmission in routine clinical practice [15,16]. The prognosis for HF with preserved systolic function is similar to that of HF with depressed ejection fraction, but there is no evidence of effective treatments in the latter group, and clinical practice guidelines offer few specific recommendations for its treatment. The current therapeutic approach for these patients is symptomatic treatment, together with control of cardiovascular risk factors and heart rate [13,14].

### Management of HF

There is good evidence in patients with HF and high risk of hospitalisation that multidisciplinary strategies based on coordination and continuity of care can reduce mortality by 25%, hospital admissions for HF by 26-44%, and admissions for any cause by 19-27%, without increasing length of stay [17]. Thus, implementation of these disease management programmes (DMPs) is recommended in the major clinical practice guidelines [13,14]. In these DMPs a case manager provides patients and their caregivers with sufficient information and support to develop and comply with a plan to control HF. The case managers also reinforce compliance with treatment and detect early signs of HF decompensation.

In Spain, several DMPs have been evaluated in elderly HF patients. Morcillo et al. randomised 70 patients with severe HF and major systolic dysfunction (NYHA III or IV and left ventricular ejection fraction < 35%), previous hospitalisation for HF and mean age 79.1 years to "usual care" versus intervention by a case manager. At 6 months follow-up there were fewer deaths, emergency department visits and hospital readmissions in the intervention group [18]. However, the exclusion criteria were very strict, so that these patients may not be representative of many patients with HF. Atienza et al., in a randomised trial in 338 patients with a mean age of 68 years, showed that a DMP in tertiary hospitals can reduce readmissions for HF by 30% [19]. Lupón et al. obtained a 49% reduction in admission of patients with HF after 1 year of applying a HF programme (non-randomised before-and-after analysis) [20]. Brotons et al. recently reported a randomised home-based intervention study in 283 patients with a mean age of 76 years, 89% of whom had NYHA class III-IV HF. They observed a considerable reduction in the combined endpoint readmission or death at 1-year follow-up; however, only 25% of the patients initially evaluated could be included because the rest either did not meet the selection criteria or refused to participate [21].

### HF management programmes in patients with advanced age and major comorbidity

The mean age of patients included in studies that have evaluated the effectiveness of DMPs in HF is 73 years, which is substantially lower than that of patients hospitalised for HF in geriatric services [22]. Most clinical trials in HF have excluded elderly (75-85 years) and very elderly (> 85 years) patients with significant functional impairment, polymedication, physical comorbidity, and preserved ventricular function. This is important because 95% of elderly HF patients have non-cardiac conditions that make their clinical management difficult and lead to increased mortality [23]. Furthermore, the process and structure of DMPs in HF vary widely, therefore it is difficult to identify which specific interventions account for their benefits [23].

For all these reasons, we do not know the effectiveness of DMPs or of their main components in geriatric patients with HF. Specifically, it is unclear whether systematic assessment and intervention on psychosocial factors can improve these patients' vital prognosis and quality of life. It is particularly important to test whether interventions useful in younger HF patients are also useful in elderly patients with predominantly preserved systolic function and some level of comorbidity [24].

Finally, little information is available on the long-term outcomes of DMPs in HF. Although the effects are maintained up to 6 months [25], it has also been observed that interruption of DMPs is accompanied by loss of their effect [26]. Thus, future evaluations of DMPs should cover a minimum period of 1 year.

### Study objectives

The main objective of the HF-GERIATRICS study is to assess the effectiveness of a DMP in elderly patients with HF and major comorbidity over 12 months. Effectiveness will be based upon hospital readmission, health-related quality of life, and mortality from any cause.

The secondary objectives are to assess the impact of the DMP on some intermediate variables such as knowledge of the disease by patients and family members, and improved HF care, which includes compliance with recommendations on lifestyles and drug treatment. This study also aims to measure the impact of the DMP on length of hospital readmissions and to identify the clinical, demographic and psychosocial characteristics of patients who benefit most from the DMP.

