### Study variables

In addition to the inclusion and exclusion criteria, four types of variables will be collected: psychosocial, biomedical, treatment prescribed, and intermediate and final outcome variables (table 2). Episodes of hospital emergency care will also be recorded. The intermediate outcome variables are knowledge of the nature and management of HF and of comorbidity, and compliance with recommendations on lifestyle and drug treatment. The final outcome variables are health-related quality of life (assessed using the Minnesota Living with Heart Failure Questionnaire [MLWHFQ]), hospital readmissions, and total mortality. The outcome variables are measured at 6 and 12 months after the DMP begins. The information is collected through interview with the patient or primary caregiver and review of the clinical record.

**Table 2 T2:** Data collected in the study

Type of data	Variables
Definition of inclusion criteria	Hospitalisation.- hospital stay at least one night. Heart failure.- Framingham and European Society of Cardiology criteria Comorbidity.- Charlson index and other (see text) [34]
Psychosocial variables	*Sex ^#^Dependence in ADLs and IADLs.- Index of Katz [35] and Lawton [35,36] ^#^Quality of life.- Minnesota Living With Heart Failure Questionnaire [37] ^#^Depression.- 15-item Yessavage depression scale [38] ^#^Cognitive function.- Lobo cognitive miniexam [39] ^#^Health literacy.- SHALSA questionnaire[40] ^#^Knowledge of disease [33] ^#^Knowledge of treatment and self-care measures [41] *Housing conditions [42] *Social support.- OARS questionnaire [43] ^#^Treatment compliance.- interview and Morisky-Green test.
Biomedical variables	*Age *Pneumococcal and influenza vaccinations *Cardiovascular risk factors.- hypertension, smoking, diabetes, hypercholesterolemia and obesity. *Factors leading to admission *Length of hospital stay *Aetiology of heart failure ^#^Functional class (NYHA) *Ejection fraction.- transthoracic echocardiography ^#^Blood sodium, NTpBNP, creatinine and glucose ^#^Blood pressure, height and weight (body mass index)
Treatment	^#^Total number of drugs ^#^Drugs.- loop and potassium-sparing diuretics, angiotensin converting enzyme inhibitors, angiotensin receptor blockers, beta-blockers, antiplatelets, anticoagulants, statins ^#^Adverse effects associated with treatment

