### Study size

In previous studies we observed that about 30% of HF patients are readmitted every 6 months [11]. These studies were conducted in hospitals and with patient's inclusion criteria different from those in the HF-Geriatrics, and within patients with less use of effective drug treatments than at present. Accordingly, under the conservative assumption that the annual frequency of readmission will be 40%, and that the frequency of readmission is similar in all study hospitals, 700 patients will need to be recruited (350 in each group) to detect, with an alpha error of 5% and a statistical power of 80%, a 20% reduction in hospital admission. This analysis assumes, as can be expected, that no patients will be lost to follow-up. A total of 700 patients also allows to detect, with an alpha error of 5% and 80% power, differences of 10 points (clinically relevant) in the MLWHFQ, assuming that patients in the control group have a mean score of 50 points on this questionnaire [11].

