### Statistical analysis

We will first verify the effectiveness of randomisation. The calculated sample size should be sufficient to assure an even balance of the predictors of the outcome variables between the intervention and control groups.

Second, we will estimate the time to readmission or death for each patient, and will obtain curves for time free of such events (Kaplan-Meier method) in the intervention and control groups. These curves will be compared using univariate methods. The effectiveness of DMP will be summarized with hazard ratios (and their 95% confidence intervals) for readmission and mortality obtained by Cox regression, using the hospital as stratification variable. Finally, if the DMP is shown to be effective, we will estimate the number of patients needed to treat (NNT) to prevent one outcome event.

For health-related quality of life, the MLWHFQ score at baseline, 6 months and 12 months will be calculated for each group in the trial. The effect of the DMP on quality of life will be estimated as the difference between groups in the change in MLWHFQ scores during the study. These differences will be accompanied by their respective 95% confidence intervals.

The analyses of the effect of DMP will be performed according to the intention-to-treat principle.

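### Effectiveness rests on three co-equal main outcomes, each at 5%, with no primary outcome and no rule for success, so the error rate of the main conclusion is not controlled

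*Protocol article*

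**What the plan says.** The main objective is to assess the effectiveness of the disease management programme (DMP) over 12 months. Under Study objectives: "Effectiveness will be based upon hospital readmission, health-related quality of life, and mortality from any cause". The Abstract gives the same three equal rank: "The main outcome variables are quality of life, hospital readmissions, and overall mortality during a 12-month follow-up". Study variables calls them final outcomes and adds: "The outcome variables are measured at 6 and 12 months after the DMP begins".

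The Study size section sizes the trial on readmission, "to detect, with an alpha error of 5% and a statistical power of 80%, a 20% reduction in hospital admission". It then turns to quality of life: "A total of 700 patients also allows to detect, with an alpha error of 5% and 80% power, differences of 10 points (clinically relevant"). Mortality has no alpha or power statement.

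The Statistical analysis section describes event-free curves for readmission or death, then "hazard ratios (and their 95% confidence intervals) for readmission and mortality obtained by Cox regression". That paragraph ends with a conditional step: "if the DMP is shown to be effective, we will estimate the number of patients needed to treat (NNT"). A separate paragraph gives the between-group difference in MLWHFQ change with its 95% interval. No section names a primary outcome, an order of testing, an adjustment, or the result that would count as success.

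**The concern.** One conclusion, that the DMP is effective, is tied to three outcomes, and the full 5% is used for more than one of them. Without a success rule, the type I error of that conclusion is undefined. A permissive reading inflates it and a strict reading does not, and the choice could be made after the results are seen.

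A split result is a realistic prospect. MLWHFQ might improve while readmission does not, and the protocol gives no agreed reading of that. MLWHFQ is a questionnaire answered by people who know whether they received the DMP. Under a permissive reading, the outcome most open to reporting bias could carry the claim alone.

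**Working it through.** **Inputs from the protocol article.** Three main outcomes (Abstract, Study objectives, Study variables). Alpha 5% for readmission and 5% for MLWHFQ (Study size). 95% intervals for all three (Statistical analysis). 350 patients per group; 40% annual readmission; 20% reduction (Study size).

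**Assumptions.** Tests are two-sided, as 95% intervals imply; the article does not state sidedness. Mortality is judged at the same 5%. The correlation between the three test statistics is not given, so a range is shown. All error rates are for the case where the DMP affects none of the three outcomes, unless stated otherwise.

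**Step 1. The stated error rate.** One two-sided test at 5% gives 5% for a false difference in either direction, or 2.5% in favour of the DMP. The stated alpha holds for the main conclusion if a single outcome decides it.

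**Step 2. Any one of three suffices.**
- Either direction, independent: 1 − 0.95³ = 0.143.
- In favour of the DMP, independent: 1 − 0.975³ = 0.073.
- With a common correlation r between three normal test statistics:

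| r | Any false difference | Any false result favouring the DMP |
|---|---|---|
| 0 | 14.3% | 7.3% |
| 0.1 | 14.2% | 7.2% |
| 0.3 | 13.6% | 6.8% |
| 0.5 | 12.5% | 6.3% |
| 0.8 | 9.8% | 4.9% |

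For correlations up to 0.5, the favourable-direction error is 2.5 to 2.9 times the nominal 2.5% (6.3/2.5 and 7.3/2.5).

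**Step 3. All three required.** The claim is false if at least one outcome has no effect, and that outcome's own test must then be significant. The error therefore cannot exceed 5% in either direction, or 2.5% in favour of the DMP. If no outcome has an effect it is far lower: at r = 0.5, about 0.3% in either direction.

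**Step 4. Only the two event outcomes count.** If MLWHFQ is left out of the rule, the any-one figures are 1 − 0.95² = 9.75% and 1 − 0.975² = 4.9% when independent, and 9.5% and 4.8% at r = 0.3.

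**Step 5. What an adjustment would cost.** Holm's strictest step uses 0.05/3 = 0.0167. With 350 per group and 40% against 32% readmission, power is 59.7% at 5% and 42.5% at 0.0167. For 40% against 30% it is 79.3% and 64.9%. The 59.7% is below the stated 80%, since 40% against 32% needs 564 per group. That is a separate matter and does not affect the error-rate arithmetic.

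**The case against.** The strongest reply is that the protocol never says any one outcome suffices, so the 14.3% belongs to a rule supplied by the reader. That is right, and it is why the figure is conditional here. It does not remove the point, because the all-three rule is not written either.

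Second, the 14.3% counts false harm as well as false benefit. A false claim of effectiveness must favour the DMP, and that risk is about 6–7%. This stands.

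Third, the conditional sentence on number needed to treat closes the time-to-event paragraph and concerns preventing an event, so it most naturally refers to readmission and mortality. This also stands: that sentence does not show that MLWHFQ alone could trigger it. The Study objectives section, however, bases effectiveness on all three.

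Fourth, details of multiplicity are commonly left to a statistical analysis plan, and a journal article is condensed. That is fair for the method of adjustment. Which outcome is primary, and what counts as success, are protocol matters. The article does not merely omit them: it ranks three outcomes equally and uses the full alpha twice.

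Fifth, equal rank may be deliberate, since the Discussion argues that quality of life deserves as much attention as hard endpoints. That is a legitimate choice, but it needs a matching error rule.

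A reader might infer three stronger points that the document does not support:
- **An error of about 26%** (1 − 0.95⁶ = 0.265), from three outcomes at two times. Measuring at 6 and 12 months is data collection, not six planned tests, and 6-month events are contained in 12-month events, so independence cannot hold.
- **A definite fourth endpoint.** The curves for readmission or death can be read as one composite or as separate curves.
- **Mortality as under-powered.** No control rate is given for the trial population. With the 25% reduction cited under Management of HF and 350 per group, power is about 41%, 52%, 62%, 79% and 92% at assumed control rates of 20%, 25%, 30%, 40% and 50%. The Background cites annual mortality above 50% in NYHA classes III and IV. All that stands is that a main outcome has no power statement.

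**Conclusion.** The point holds in a conditional form. The protocol names neither a primary outcome nor a success rule for its one main objective, so the 5% error is not secured for the main conclusion.

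The size depends on the unwritten rule. Under any-one-suffices, at correlations up to 0.5, it is 12.5–14.3% for at least one false difference and 6.3–7.3% for a false result favouring the DMP, against 5% and 2.5%. Under all-three-required it is below 5%. These figures assume two-sided 5% tests on each outcome and an equal correlation between them. It would be wrong to say that the plan has a 13–14% chance of falsely declaring the DMP effective. That needs a rule the protocol does not state, and it counts errors in both directions.

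**What to change.** Name one primary outcome at 12 months. Hospital readmission is the most consistent choice, because the Study size section bases the 700 patients on it. Readmission or death would also serve, provided its assumed rate, effect and power are then stated; the article gives none of these for the composite. Define effectiveness, including the condition for calculating the number needed to treat, as success on that outcome.

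Test the remaining main outcomes at 5% in a fixed order stated in advance. Alternatively, if quality of life is meant to have equal standing, keep all three co-equal and apply a Holm adjustment. Treat 6-month results as supportive in either case.

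The change is to protocol wording only. Under the fixed order, later outcomes carry no confirmatory claim once the primary, or an earlier outcome in the order, fails. Under Holm, each test has somewhat less power; the 0.0167 figures in the working show the loss for readmission at the strictest step.

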## Methods/Design

### Design

The HF-GERIATRICS study is a trial in elderly patients who are admitted with a primary diagnosis of HF in acute care units of eight geriatric services in Spain. Patients are assigned randomly to a DMP (intervention group) or to receive usual care (control group). Randomisation is stratified by hospital and is conducted with concealment of the randomisation list. The two trial groups are followed for 12 months.

The project has been approved by the clinical research ethics committee of all participating hospitals (Comité de Etica y Ensayos Clínicos (CEIC) de Galicia, CEIC del Complejo Hospitalario de Caceres, CEIC del Hospital Universitario La Paz, CEIC del Complejo Universitario de Albacete, CEIC del Hospital Universitario de Guadalajara, CEIC del Hospital Central de Asturias, CEIC del Hospital Universitario de Getafe, CEIC del Hospital Universitario de San Carlos, Spain).

### Study participants

The study will include patients aged 75 years or over who are admitted with a primary diagnosis of HF according to the European Society of Cardiology and Framingham criteria [14,27]. Each patient must also meet at least one of the following comorbidity criteria: Charlson index ≥ 3 (regardless of age), dependence in ≥ 2 basic activities of daily living, prescription of ≥ 5 drugs, emergency hospitalisation in the last 3 months, active treatment for ≥ 3 diseases, limitations in daily life due to visual or hearing loss, cognitive impairment, Parkinson's disease, diabetes mellitus, chronic obstructive pulmonary disease (COPD), anaemia or constitutional syndrome whose causes have not been determined previously.

Exclusion criteria are terminal or rapidly fatal disease and life expectancy of less than 6 weeks, severe functional or cognitive impairment preventing patients from understanding their illness and lack of a caregiver who agrees to participate in the study, patients waiting for cardiac surgery, those who cannot be followed up (e.g., due to change of address), and institutionalised persons for whom a primary caregiver cannot be identified.

### Identification of participants, informed consent and randomisation

In each hospital a case manager with a degree in health sciences and special training in HF will identify and register cases admitted for HF each day by reviewing the diagnoses of those aged ≥ 75 years admitted in the acute care unit of the geriatric service. The case manager will then assess each patient and carry out the following activities:

i- Verify the study inclusion and exclusion criteria.

ii- Inform patients (verbally and in writing) and their caregivers (when considered necessary and with the patient's consent) of the characteristics of the DMP and confirm their agreement to participate by asking them to sign the informed consent document.

iii- Assign the patient to the intervention or control group. Randomisation will be conducted independently in each centre. Consecutively numbered envelopes, containing the group to which each patient should be assigned, will be used for this purpose. The envelope will be opened only at the time of patient assignment, to assure concealment of the randomisation list.

iv- Coordinate patient assessment, record the information in the case report form, and transcribe the information to a computerized database.

